### 2.3. Participants

There are two participant groups in this study: parents and MacKillop Family Services staff.

Parents: Parents either have children (0–17 years of age) who are vulnerable to removal from the home due to a child protection assessment of risk, have children already in OOHC, or are pregnant and have had ‘unborn’ reports to child protection. These parents may have multiple factors that are contributing to their risk profile including recent family violence, drug or alcohol misuse, fragile mental health, court orders and justice involvement among others. Parents can vary in age and may be adolescent parents or those who are currently living in a care arrangement (foster, kinship, or residential OOHC). Sample size calculations have been conducted using G*Power based on the NCFAS as this measure goes across most efficacy outcomes. For an analysis of variance test with the alpha set at 0.005, correlations between repeated measures set at 0.50 and power of 0.95, a total sample of 98 families will be required. To allow for a 25% rate of non-completion, at least 123 families will be recruited. During the study period, it is expected that up to 1100 families will engage in MacKillop’s FPR program. Based on similar research, we expect a high number of families to consent to participate in the study [25], therefore, it is expected that this sample size requirement will be met by the end of the study period.

MacKillop Family Services Staff: MacKillop directors, managers, team leaders and practitioners involved in the delivery of the FPR program are eligible to participate in interviews or focus groups about their experiences of implementing the program. Only staff who consent will take part in the research evaluation.

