#### 3.1.4. FPR Effectiveness in Reducing Reports to Child Protection and Subsequent Placement into OOHC

To understand if the MacKillop Family Services FPR has been successful at reducing family involvement with child protection and preventing children from entering/re-entering OOHC, three types of linked data from the government are being sourced, subject to approval: (1) reports made to child first, or other child protection organisations who use the Client Relationship Information System (CRIS) system, about FPR children and parents in the six months before participating in the FPR, the six months during and then six months after program closure; (2) number of times children have been in OOHC in the 12 months post FPR participation; (3) time to reunification after removal; or (4) time to removal/re-removal.

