## 4. Analytical Considerations

The primary quantitative outcome of this study is to examine the degree to which there are improvements in psychosocial outcomes among families who engage in the program. All completed questionnaires will be de-identified by a specific data aggregation worker who will assign a unique ID code (e.g., FPR003) to each family so that their data remain anonymous to the research team. Descriptive statistics will be calculated based on administrative and demographic data sourced from the referral form. Main caregiver complexity will be determined using the ACEs survey and the number of ACEs will be calculated. A series of paired sample t-tests (repeated measures) will be used to compare participants’ mean differences on the measures at the beginning and end of the program. Analysis of Variance will be employed to review the number of reports before, during and after the program to determine any statistical differences. The number of care episodes and time to reunification will be analysed descriptively. All analyses will be performed using the Statistical Package for the Social Sciences (SPSS) software.

All qualitative data will be analysed using thematic analysis [41]. Data collection and analysis will occur concurrently so that data saturation can be adequately assessed. All audio recordings will be transcribed verbatim and systematically coded. Following in-depth review of the coded data, independent themes will be identified and developed based on recurrent content reflecting the different aspects of program implementation. The process of refining and reviewing themes will be an iterative process until themes are representative of the most pertinent and recurrent aspects of the data.

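### The ANOVA on raw child-protection report counts ignores where the child was living, so removals and reunifications can shift the result and it cannot be read alone as the programme's effect

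*Protocol article*

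**What the plan says.** Section 3.1.4 requests linked government data to judge whether the programme "has been successful at reducing family involvement with child protection and preventing children from entering/re-entering OOHC". The first item is reports "about FPR children and parents in the six months before participating in the FPR, the six months during and then six months after program closure". The same section also requests the number of OOHC episodes in the 12 months after participation, time to reunification, and time to removal or re-removal, all subject to approval.

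Section 4 fixes the analysis of the reports: "Analysis of Variance will be employed to review the number of reports before, during and after the program to determine any statistical differences". For placement it says: "The number of care episodes and time to reunification will be analysed descriptively".

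Section 2.3 defines a single parent group. It takes in parents with children "who are vulnerable to removal from the home due to a child protection assessment of risk", parents who "have children already in OOHC", and pregnant parents with an unborn report. The article does not restrict, stratify or adjust the report counts by placement or by type of entry.

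**The concern.** The F test asks whether mean counts are equal in three windows. Equal counts mean an unchanged tendency to be reported only if the opportunity to be reported is similar in each window. Removal and reunification are the programme's own outcomes, and both can change that opportunity.

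A child removed during the programme spends less time in parental care afterwards, so a preservation failure may lower the count. A child who starts in care and goes home is exposed to parental care again, so a successful reunification may raise it. With both kinds of family in one analysis, the two shifts can also offset each other and leave a null result that hides both.

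This is separate from regression to the mean after referral: it persists even if the at-home report rate never changes. It matters because the ANOVA is the only inferential test named for the linked child-protection data, and section 6 says significant improvements would support national scale-up.

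**Working it through.** **Inputs from the article.** Three six-month windows (3.1.4); ANOVA on counts (4); pooled entry groups (2.3); 98 families, the sample size before allowance for non-completion (2.3). The article gives no expected count or power for reports, so there is no stated figure to reproduce. The 98 was derived for the NCFAS and serves here only as a plausible size.

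**Assumed, because not given.** Share of preservation children removed, p; in-care report rate as a fraction of the at-home rate, q; report rate of 1 or 2 per six months.

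**Step 1: expected counts, preservation.** Hold the at-home rate constant. If a share p is away for the whole after-window,

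after/before = 1 − p(1 − q).

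- p = 0.20: 0.80 (q = 0), 0.90 (q = 0.5), 1.00 (q = 1).
- p = 0.30: 0.70 (q = 0), 0.85 (q = 0.5), 1.00 (q = 1).

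**Step 2: expected counts, reunification.** For a child at home for a share h of the before-window and for all of the after-window,

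after/before = 1 / [h + (1 − h)q].

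- h = 0: 4.0 (q = 0.25), 2.0 (q = 0.5), 1.0 (q = 1).
- h = 0.5: 2.0 (q = 0), 1.33 (q = 0.5), 1.0 (q = 1).

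**Step 3: a mixed sample.** Take 70% preservation families with 20% of children removed, 30% reunification families with half returned home, a rate of 1 per window, and q = 0.

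- Before: 0.70 × 1 + 0.30 × 0 = 0.70.
- After: 0.70 × 0.80 + 0.30 × 0.50 = 0.56 + 0.15 = 0.71.

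The overall mean barely moves although both groups have changed.

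**Step 4: false-positive rate of the ANOVA.** Simulation with 98 families, one child standing for each family, gamma-Poisson counts (between-family coefficient of variation 0.5), removal at a uniform time in the during-window with no return, and repeated-measures ANOVA with Greenhouse-Geisser correction at a nominal 5%. Each range covers rates of 1 and 2 reports per six months and variation between repeated runs.

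| In-care rate ÷ at-home rate (q) | 20% removed | 30% removed |
|---|---|---|
| 0 | 22–38% | 47–73% |
| 0.5 | 8–13% | 14–26% |
| 0.75 | 4–7% | 6–10% |
| 1 | about 5% | about 5% |

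With no removals the rate is about 5%. Section 2.3 uses an alpha of 0.005 for sample size. At that level 30% removed gives about 16–40% at q = 0 and 3–6% at q = 0.5, against a nominal 0.5%.

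**Step 5: do the planned placement data repair this?** Only in part. They are described separately from the reports. The OOHC episode count covers 12 months after participation, so it neither matches the six-month report windows nor includes a removal during the programme.

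**The case against.** A reader might infer that removals necessarily lower the count and reunifications necessarily raise it. The documents do not support that. No in-care report rate is given. The reports concern parents as well as children, and a parent or a sibling still at home can generate reports after one child is removed. At q = 1 the effect disappears, so q = 0 is an extreme case. The reunification shift is likewise largest only if the child was in care throughout the six months before intake. The article says no more than that children are already in care, and a recent removal would bring the reports that led to it into the before-window.

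A reader might also infer that the plan hides removals. It does not: OOHC episodes and time to removal are requested under the same heading as reports, and care episodes are to be described.

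Three further points have weight. Total reports are a direct answer to a question about family involvement with child protection, whereas reports per day at home answer a different one. Section 4 makes psychosocial improvement the primary quantitative outcome. Sections 2.2 and 5 already acknowledge the limits of an uncontrolled pre-post design.

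These points reduce the certainty and size of the concern. They do not make the pooled test interpretable alone, because the article reads total reports as evidence of success while placement is free to move them in either direction.

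**Conclusion.** The point stands in conditional form. The article fixes the outcome, the windows, the test and the purpose, and it pools entry groups for which the same change in count can mean opposite things. If in-care reporting is lower than at-home reporting, neither a significant nor a null ANOVA result shows by itself what the programme did to child-protection involvement.

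The size is uncertain. With 20 to 30% removed, false positives at a nominal 5% run from about 22–73% with no in-care reports, through 8–26% at half the at-home rate and 4–10% at three quarters, to about 5% at equal rates. These figures rest on assumed removal shares and report rates, a constant at-home rate, one child per family and 98 families. The analysis should be changed, but the consequence is limited to one component of the effectiveness objective.

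**What to change.** In section 4:

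1. Analyse report counts separately for preservation, reunification and unborn entry groups, using entry status known at referral.
2. Present each group's counts by placement status, with removals and reunifications over the same three windows.
3. State that a fall in reports will not be interpreted as success without those placement results.
4. Where the linked data give placement dates, add as a sensitivity analysis a Poisson or negative binomial GEE with days in parental care as the offset. Label it as answering a different question from total reports.
5. State that windows with no days at home are not informative in that model. For a reunification child in care for the whole six months before intake, this removes the before-window.

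**Cost.** Items 1 to 3 need mainly wording, plus removal and reunification dates aligned to the report windows. Item 4 is not free of new data: section 3.1.4 does not request placement days in the six months before intake, so these must be added to the linkage request or taken from the connection form. Strata will be smaller and intervals wider.

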## Abstract

International evidence supports the effect of intensive family preservation and reunification services in preventing children’s placement in out-of-home care (OOHC). Evidence within Australia is scarce. This protocol paper describes a hybrid effectiveness-implementation evaluation of the Victorian Family Preservation and Reunification (FPR) Response implemented by MacKillop Family Services. Participants include families engaged in the program and staff involved in program delivery. A pre-post study design will be used to assess the effectiveness of the FPR in improving family outcomes from intake to closure, including: (i) parenting knowledge, skills, and capability; (ii) family safety and home environment; (iii) child development, adolescent behaviour, education attendance and attachment; (iv) connection to services; and (v) prevention of children from entering or re-entering OOHC. Interviews and focus groups will be conducted with staff to evaluate the program’s fidelity, reach, feasibility, acceptability, and enablers and barriers to implementation. Quantitative data will be analysed using descriptive statistics and a series of paired-samples t-tests and F tests to examine changes in outcomes over time; thematic analysis will be used for qualitative data. If the FPR can yield significant improvements in families’ outcomes, this would provide strong support for its scale-up across Australia, to better support vulnerable families.

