## 6. Conclusions

The current study is necessary and critical for generating Australian evidence regarding the effectiveness of an intensive family service program that aims to preserve or reunify families through the provision of assertive outreach support. Importantly, if the program is found to be well-implemented and yields significant improvements in families’ outcomes from baseline to closure, then this would provide strong support for the scale-up and dissemination of the Response across Australia. In turn, this could begin to foster the intergenerational outcomes that many of the target families currently experience.

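### Child-protection reports are tested for any difference over three periods with no deciding comparison, so a change confined to the programme period can give a significant F when reports after closure equal those before

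*Protocol article*

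**What the plan says.** Section 3.1.4 of the protocol article sets out why linked government data are sought: to learn whether the programme has been "successful at reducing family involvement with child protection and preventing children from entering/re-entering OOHC". Reports are to be counted "in the six months before participating in the FPR, the six months during and then six months after program closure". Table 1 lists child protection notifications among the effectiveness outcomes.

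Section 4 gives the analysis in one sentence: "Analysis of Variance will be employed to review the number of reports before, during and after the program to determine any statistical differences". The paired t-tests in the same section are assigned to the measures taken at the start and end of the programme. Care episodes and time to reunification are to be described only. The ANOVA on reports is therefore the only inferential test that the article states for the linked child-protection data.

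No significance level is given for this test. The only one in the article is in section 2.3, for the sample size based on the NCFAS: "analysis of variance test with the alpha set at 0.005".

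**The concern.** The question has a direction and the stated test has none. An F test over three periods has two numerator degrees of freedom and covers three pairwise comparisons: before with during, before with after, and during with after. These can point in different directions, and the article does not say which one decides.

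The middle window also differs in kind from the other two. Sections 1.2 and 3.1.4 together place it in a period of intensive home visiting, with Child Protection attending care team meetings. Reports could fall while support is in place, or rise because the family is observed more closely. The article claims neither, but either is plausible, and either can make F significant with no change from before to after.

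At stake is the reading of the one test on child-protection involvement. Section 1.1 says that the model assumes a permanent shift in families' trajectory away from the child protection system. A dip that fully rebounds after closure would not show that, yet it could be reported as a statistical difference.

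**Working it through.** **1. The plan's own figure.** Section 2.3 gives alpha 0.005, power 0.95, correlation 0.50 between repeated measures, and 98 families. It states no effect size. For a within-family F test with m periods, the noncentrality is λ = f²·n·m/(1−ρ), on (m−1) and (n−1)(m−1) degrees of freedom. With m = 3 and an assumed f = 0.20, λ = 0.04 × 98 × 3 / 0.5 = 23.52 on 2 and 194 df, and the smallest n that reaches 0.95 power is exactly 98. The same formula can therefore be used for the reports.

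**2. Only the middle period moves.** Let the period means be (0, −d, 0) in SD units. The SD of the three means is f = d·√2/3, so λ = (2/9)·d² × 98 × 3 / 0.5 = 130.7·d². The probability of a significant F with 98 families is:

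| d (SD) | alpha 0.05 | alpha 0.005 |
|---|---|---|
| 0.2 | 52% | 21% |
| 0.3 | 87% | 61% |
| 0.4 | 99% | 92% |
| 0.5 | about 100% | 99% |

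The true before-after change is zero in every row, so a before-after contrast would be significant at about its nominal rate.

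**3. The same check on counts.** The article gives no report rate, dispersion or size of change, so these are assumptions: 98 families, mean 1 report per window before the programme, Poisson counts with a gamma family effect of variance 0.5 shared across windows, and 20,000 simulated studies per row. The omnibus test is the repeated-measures F; the contrast is the paired before-after t-test.

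| Before/during/after | Omnibus, 0.05 | Contrast, 0.05 | Omnibus, 0.005 | Contrast, 0.005 |
|---|---|---|---|---|
| 1.0/1.0/1.0 | 5% | 5% | 0.5% | 0.4% |
| 1.0/0.6/1.0 | 90% | 5% | 63% | 0.4% |
| 1.0/0.8/1.0 | 30% | 5% | 7–8% | 0.5% |
| 1.0/1.5/1.0 | 91% | 5% | 69% | 0.5% |

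**4. Sensitivity.** Changing the shared family variance to 0.3 or 1.0 hardly alters the 40% dip (89–90% at 0.05). Overdispersion specific to each period matters much more. With period-level variance 0.5 the 40% dip falls to 69% at 0.05 and about 31% at 0.005; with variance 1.0 it falls to 54% and 17%.

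**5. Power when there is a real before-after fall (level 0.05).**

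| Before/during/after | Omnibus | Contrast |
|---|---|---|
| 1.0/0.85/0.7 (gradual) | 51% | 61% |
| 1.0/1.0/0.7 (after closure only) | 63% | 61% |
| 1.0/0.7/0.7 (complete by the programme period) | 65% | 61–62% |

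**The case against.** The strongest reply is that section 4 is a condensed sentence. It does not say that the ANOVA stands alone, and pairwise follow-up may be set out in a fuller protocol or analysis plan that is not shown. That is fair, and a reader should not infer that follow-up comparisons are ruled out. What stands is the stated pairing of a non-directional three-period test with a directional question. Adding all pairwise tests would not cure it unless one of them were named as deciding.

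A reader might also take the 90% as a false-positive rate. It is not: with means 1.0/0.6/1.0 the period means truly differ and F is right to reject. Harm arises only if the result is reported as a reduction although the three means show a rebound.

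A reader might further infer that a significant F on reports would trigger the scale-up claim. The documents do not support this. Section 6 speaks of a programme that "yields significant improvements in families’ outcomes from baseline to closure, then this would provide strong support for the scale-up". That wording concerns improvement up to closure, is itself directional, and is joined to good implementation. The report windows run six months past closure, and section 4 names psychosocial outcomes as primary.

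Finally, section 3.1.4 does not say that only before-after change counts, and fewer reports during the programme may be of interest in their own right. This is a good reason to keep the other two contrasts as secondary.

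**Conclusion.** The point holds in a limited form. The stated test can be significant through a change confined to the programme period, so it does not by itself show whether involvement was reduced once the programme ended. How often this would happen depends on inputs that the article does not give. At 0.05 the range shown runs from about 30% for a 20% dip to about 90% for a 40% dip, and from 7–8% to 63% at 0.005. All of these are lower with period-level overdispersion.

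The case does not rest on power, which is mixed: about 10 points in favour of the contrast for a gradual fall, and a few points against it if the fall is complete by the programme period. Severity is minor to moderate. Reports are a named effectiveness outcome and this is their only stated test, but they are not the primary outcome, and the period means would presumably be visible in any report.

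**What to change.** Replace the ANOVA sentence in section 4 with wording such as: 'The main comparison for child-protection reports is the within-family change from the six months before the programme to the six months after closure, tested as a single 1-df contrast and reported as an estimate with its confidence interval. Only a lower rate after than before counts as evidence of a lasting reduction. The before-during and during-after contrasts are secondary and are labelled as such.' State the significance level for this contrast in the same place.

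The change needs no new data and no more families, and should be made before the linked data are analysed. It has two costs. A reduction seen only during the programme can no longer be the main result for reports. Power is also slightly lower in some patterns: about 65% to 61–62% for means 1.0/0.7/0.7 at level 0.05.
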